## Abstract

**Background:**

The French organized population-based cervical cancer screening (CCS) program transitioned from a cytology-based to a human papillomavirus (HPV)–based screening strategy in August 2020. HPV testing is offered every 5 years, starting at the age of 30 years. In the new program, women are invited to undergo an HPV test at a gynecologist’s, primary care physician’s, or midwife’s office, a private clinic or health center, family planning center, or hospital. HPV self-sampling (HPVss) was also made available as an additional approach. However, French studies reported that less than 20% of noncompliant women performed vaginal self-sampling when a kit was sent to their home. Women with lower income and educational levels participate less in CCS. Lack of information about the disease and the benefits of CCS were reported as one of the major barriers among noncompliant women. This barrier could be addressed by overcoming disparities in HPV- and cervical cancer–related knowledge and perceptions about CCS.

**Objective:**

This study aimed to assess the effectiveness of a chatbot-based decision aid to improve women’s participation in the HPVss detection-based CCS care pathway.

**Methods:**

AppDate-You is a 2-arm cluster randomized controlled trial (cRCT) nested within the French organized CCS program. Eligible women are those aged 30-65 years who have not been screened for CC for more than 4 years and live in the disadvantaged clusters in the Occitanie Region, France. In total, 32 clusters will be allocated to the intervention and control arms, 16 in each arm (approximately 4000 women). Eligible women living in randomly selected disadvantaged clusters will be identified using the Regional Cancer Screening Coordinating Centre of Occitanie (CRCDC-OC) database. Women in the experimental group will receive screening reminder letters and HPVss kits, combined with access to a chatbot-based decision aid tailored to women with lower education attainment. Women in the control group will receive the reminder letters and HPVss kits (standard of care). The CRCDC-OC database will be used to check trial progress and assess the intervention’s impact. The trial has 2 primary outcomes: (1) the proportion of screening participation within 12 months among women recalled for CCS and (2) the proportion of HPVss-positive women who are “well-managed” as stipulated in the French guidelines.

**Results:**

To date, the AppDate-You study group is preparing and developing the chatbot-based decision aid (intervention). The cRCT will be conducted once the decision aid has been completed and validated. Recruitment of women is expected to begin in January 2023.

**Conclusions:**

This study is the first to evaluate the impact of a chatbot-based decision aid to promote the CCS program and increase its performance. The study results will inform policy makers and health professionals as well as the research community.

**Trial Registration:**

ClinicalTrials.gov NCT05286034; https://clinicaltrials.gov/ct2/show/NCT05286034

**International Registered Report Identifier (IRRID):**

PRR1-10.2196/39288

## Introduction

### Background

In France, there were an estimated 2920 new cervical cancer (CC) cases and 1117 related deaths in 2018, with marked geographical disparities within regions [1]. A decline in CC incidence and mortality rates was observed during the period of 1990 to 2018, although this was less pronounced in recent years [1]. The prognosis of CC is deteriorating in France, with a 5-year survival rate after diagnosis decreasing from 68% in 1989 to 1993 to 62% in 2005 to 2010 [2]. During the period of 2018 to 2020, the national triennial coverage rate was 59.2%, with a strong geographical disparity within French departments, ranging from 11.8% to 65% [3]. The national screening coverage rate appeared relatively stable since 2012 across the age groups and declined markedly in women older than 50 years, down to 44.2% in women aged 60 to 65 years [4].

The French organized population-based CC screening (CCS) program shifted from a cytology-based to a human papillomavirus (HPV)–based screening strategy in August 2020. HPV testing is offered every 5 years, starting at the age of 30 years. In the new program, women are invited to have the HPV test at a gynecologist’s, primary care physician’s, or midwife’s office, a private clinic or health center, family planning center, or hospital. A reminder letter is sent to noncompliant women after 12 months from the date of the first screening invitation.

HPV self-sampling (HPVss) was also made available as an additional approach to recall noncompliant women 1 year after the initial invitation [5]. There is a strong body of evidence to support the usefulness of HPVss in increasing participation of hard-to-reach women in screening programs [6,7]. In France, 2 randomized controlled trials (RCTs) have been conducted to evaluate home-mailing of HPVss kits directly to noncompliant women in 2 regions [8,9]. Home-based HPVss testing was accepted among French women and increased participation in CCS compared with a recall letter: 18.3% versus 2.0% [8] and 22.5% versus 11.7% [9], respectively, among nonattendees. Some concerns remain regarding adherence to further follow-up among high-risk women with positive test results. The French studies reported substantial variation in compliance with follow-up among HPVss-positive women (41% vs 92%) [8,9]. These studies also found that less than 20% of noncompliant women performed vaginal self-sampling when an HPVss kit was sent to their home. Women are concerned about the self-test’s effectiveness and are afraid of hurting themselves when collecting the sample [10].

In France, women older than 50 years, those with unfavorable socioeconomic status, those living in disadvantaged and in low-medical-density areas, those with long-term disease, and those covered by *complementary health insurance* are more likely to not participate in CCS [11]. Lack of information about CC and the benefits of CCS were reported as two of the major barriers among noncompliant women [12-14]. These barriers could be addressed by overcoming disparities in HPV- and CC-related knowledge and perceptions about CCS.

Studies showed that decision aids improve knowledge, decrease decisional conflict, and increase the proportion of individuals who are active in the decision-making process [15,16]. Decision aids must be carefully established, tested and validated by users, and meet their needs [17]. Standard information materials, even with simple text and design, are not an appropriate communication tool for individuals with low health literacy [18]. In contrast, animated educational videos were found to be the best way to communicate complex health information to such individuals [19]. Health literacy is defined as “[people’s ability] to make judgements and take decisions in everyday life concerning healthcare, disease prevention and health promotion to maintain or improve their quality of life” [20]. Low health literacy is prevalent among people who are older, less educated, low-income, have chronic conditions, and do not speak the native language of the country where they live [21]. In France, the prevalence of low health literacy was estimated to be 51% (95% CI 34%-67%) [22].

One of the useful innovative tools being used to self-administer web-based health information is the chatbot. Chatbots, as artificial intelligence (AI) devices, are applications that provide information or services through interactions with users [23]. To our knowledge, no study has evaluated the usefulness of AI-based chatbot services to empower women and democratize the decision-making process about CCS. This study will be the first to develop and test a chatbot-based decision aid tailored to women with lower education attainment. Previous systematic reviews have shown that no RCTs have examined shared decision-making in CCS programs [16,24]. This paper describes the objectives and protocol of the cluster randomized trial (cRCT) using the Standard Protocol Items: Recommendations for Interventional Trials–Patient-Reported Outcomes (SPIRIT-PRO) guidelines.

### Objectives and Endpoints

The primary objective of this AppDate-You study is to assess the effectiveness of a chatbot-based decision aid to improve women’s participation in the HPVss detection–based CCS care pathway, in particular among noncompliant women living in disadvantaged areas in Occitanie Region, France.

The main secondary objectives are to evaluate the impact of the intervention on (1) the detection rate of cervical intraepithelial neoplasia grade 2+, (2) the intervals between the dates of the reminder letter and the HPVss test report and between the dates of sending a positive HPV test result and performing liquid-based cervical cytology (triage test), and (3) the efficiency (cost-effectiveness) of the intervention.

## Methods

### Study Design

A 2-arm cRCT will be conducted (Figure 1). A cluster is defined by aggregated units for statistical information (*Ilots Regroupés pour l’Information Statistique;* IRIS), corresponding to 2000 inhabitants per unit. Only IRIS classified as 4 or 5 (the most disadvantaged IRIS) in accordance with the French version of the European Deprivation Index will be included [25]. The study will be nested within the French CCS program in the Occitanie Region. Recruitment of women will start in January 2023 and end in December 2024, and HPVss-positive women will be followed-up for 12 months after the last participants are recruited.

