### Sample Size

The sample size involved estimation of the number of clusters (IRIS) using a composite outcome, “well-managed” women, which is defined as those women who completed a valid HPVss test and were either advised of a negative result (in the case of HPVss-negative women) or completed the assessment (in the case of HPVss-positive women), and, where necessary, treatment pathway. The following assumptions were considered:

Expected average cluster size of 250 eligible women; this is an estimate of the number of women in the target age range (30-65 years) within a cluster of 2000 people, based on the population pyramid of ages in the Occitanie Region.Expected proportion of overall well-managed women in the control group of 15%.Expected absolute increase of 10% in the proportion of overall well-managed women in the experimental group.Coefficient of variation taking into account the possibility of varying cluster sizes of 1.2 (arrived at because of the wide level of dispersion around the mean cluster size) [26].A 10% precision in the proportion of overall well-managed women, which would lead to a 0.029 intracluster correlation using a beta-binomial model [27].A power of 80% and a 5% 2-tailed significance level.

Under the aforementioned assumptions, the required number of clusters to randomize in each arm would be 10 (total: 20 clusters). However, if subgroup analyses are to be performed, stratifying on general population density, medical density of the department (high or low), and setting of the community (rural or urban), taking into consideration these α adjustments (α=.3125% [2.5%/8]) for each of the subgroup analyses in order to be able to remain with a 5% 2-tailed significance level for the overall effect, approximately 16 clusters in each arm (32 clusters in total) will be required for the subgroup analyses.

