### HPV Test Analysis and Management of Results

Participating women in both groups will be asked to send the samples via regular mail to a centralized laboratory using the postage-paid envelope. The results will be communicated to the women, their primary care physician, and the CRCDC-OC generally within 2 weeks after the self-collected sample arrives at the centralized laboratory. Women with negative results will be advised to repeat CCS after 5 years. HPVss-positive women will be invited to consult their primary health physician, who will explain what a positive HPVss test result means and suggest further investigations in accordance with national guidelines [28].

HPVss-positive women will be referred for liquid-based cervical cytology triage:

HPVss-positive women with a cytological diagnosis of atypical squamous cells of undetermined significance or worse will be referred for colposcopy.HPVss-positive women with a normal cytological diagnosis will be advised to undergo HPV testing 1 year later. If this triage HPV test, performed 1 year later, yields positive results, colposcopy should be performed; if this triage HPV test yields negative results, another HPV test should be offered 5 years later.

For women with an uninterpretable HPV test, a new HPVss collection kit will be sent to them. If the second HPV test result is also uninterpretable, the women will be advised by mail to have an HPV test with a health professional as soon as possible.

The CRCDC-OC will track the HPVss-positive women to investigate whether they receive follow-up procedures in accordance with national recommendations and will recall women or providers, if necessary.

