### Primary Study Outcomes

The study has 2 primary outcomes: (1) the proportion of screening participation within 12 months among women recalled for CCS and (2) the proportion of HPVss-positive women who are “well-managed” as stipulated in the French guidelines. Both proportions will be compared between experimental and control groups, taking into account the stratification by age group, place of residence, and type of health insurance.

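### A single calendar cut-off gives HPVss-positive women between almost none and 36 months of follow-up for the second primary outcome, and the last women recalled cannot reach the 1-year retest

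*Protocol article*

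**What the plan says.** All statements are in the protocol article.

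- **Study Design:** recruitment runs over 24 months, from January 2023 to December 2024. On the end of follow-up the section states: "HPVss-positive women will be followed-up for 12 months after the last participants are recruited". The end of follow-up is therefore one calendar date, about December 2025, and not a period counted from each woman's own recall or result.
- **Primary Study Outcomes:** the first primary outcome is "the proportion of screening participation within 12 months among women recalled for CCS". The second is "the proportion of HPVss-positive women who are “well-managed” as stipulated in the French guidelines". The second has no time window.
- **HPV Test Analysis and Management of Results:** results are issued "generally within 2 weeks after the self-collected sample arrives at the centralized laboratory". Positive women go to triage cytology. Then "HPVss-positive women with a normal cytological diagnosis will be advised to undergo HPV testing 1 year later". A positive result at that later test leads to colposcopy, with no time limit given.
- **Sample Size:** a composite also called well-managed is defined. For positive women it requires that they "completed the assessment (in the case of HPVss-positive women), and, where necessary, treatment pathway". This composite covers HPV-negative women as well, so it is not the same quantity as the second primary outcome.
- **Statistical Analysis:** effects on primary and secondary outcomes are to be assessed by logistic regression, with Bayesian software used to model missing data.

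**The concern.** The second primary outcome asks whether a positive woman received the care that the guidelines call for. Answering that requires watching each woman long enough for the steps to fall due. Here the watching time depends on when she was recalled and how long she took to return a sample. A woman recalled at the end of recruitment who tests late still counts as a participant, but has almost no time left even for triage cytology. A woman recalled at the start has up to three years.

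A proportion or logistic model applied to all positive women at that cut-off pools these unequal periods. The result would mix three things: management after a positive result, recall date, and time to testing. The third matters most for the comparison, because the decision aid may change how quickly women test. The plan itself compares reminder-to-report intervals between arms as a secondary outcome.

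**Working it through.** The plan gives no follow-up figure per woman to reproduce, and its sample-size calculation does not bear on this point. The check is a timeline.

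**Inputs from the document**
- Recall: month 0 (start of January 2023) to month 24 (end of December 2024), reading recruitment as the date of recall.
- Cut-off: 24 + 12 = month 36.
- First test: t = 0 to 12 months after recall.
- Result turnaround: about 2 weeks, taken as 0.5 month.
- Retest: 12 months after normal cytology.

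**Assumptions, not in the document**
- Recall spread evenly over the 24 months.
- Delay c from result to cytology: 0 or 2 months.

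**Step 1: follow-up after the first test.** With r = months from recall to end of recruitment (0 to 24), follow-up = 12 + r − t.
- Recalled last, tests at month 12: 12 + 0 − 12 = 0 months.
- Recalled last, tests at once: 12 + 0 − 0 = 12 months.
- Recalled first, tests at once: 12 + 24 − 0 = 36 months.

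This spread exists whether or not the retest is scored.

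**Step 2: time needed to reach the retest, from recall.** Need = t + 0.5 + c + 12.
- Fastest case: 0 + 0.5 + 0 + 12 = 12.5 months, against 12 available to the last woman recalled.
- Test at month 12, no cytology delay: 12 + 0.5 + 0 + 12 = 24.5 months.

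**Step 3: share of normal-cytology women whose retest falls after the cut-off.** The retest is missed when 12 + r < t + 0.5 + c + 12, that is when r < t + c + 0.5. With r even over 0 to 24, the share is (t + c + 0.5)/24.

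| First test (t) | Delay to cytology (c) | Share beyond cut-off |
|---|---|---|
| 0 | 0 | 0.5/24 = 2% |
| 3 | 2 | 5.5/24 = 23% |
| 6 | 2 | 8.5/24 = 35% |
| 12 | 0 | 12.5/24 = 52% |
| even over 0–12 (mean 6) | 0 | 6.5/24 = 27% |
| even over 0–12 (mean 6) | 2 | 8.5/24 = 35% |

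The first row rests entirely on the result turnaround. A faster result would lower any row by at most 0.5/24 = 2 percentage points. These shares stop at the retest; a colposcopy after a positive retest would need further time.

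**Step 4: sensitivity to time to testing.** In the same formula, one month's difference in t moves the share by 1/24, about 4 percentage points among normal-cytology women. This illustrates how a difference between arms could arise. It is not an estimate of one.

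**The case against.** The strongest case on the other side has four parts.

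1. **The retest may not be scored.** The second primary outcome refers to national guidelines that are not reproduced. A woman with normal cytology whose retest is not yet due has missed no step of the pathway. The follow-up interval that the plan measures in positive women ends at triage cytology. *This stands in part.* The text does not settle the reading. If the outcome is met at normal cytology, the problem shrinks a good deal, but late testers still run out of time for cytology, colposcopy or treatment.

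2. **This belongs in the analysis plan.** A window per woman and a rule for women not yet due are often set there. *This stands for the estimator.* It does not stand for the follow-up end date, the participation window and the pathway, which the article itself fixes and which do not fit together. An analysis plan cannot use data that fall after the extraction.

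3. **Missing outcomes will be modelled.** The article does say that missing data will be modelled. It does not say that women not yet due are treated as missing.

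4. **The shares concern a subgroup.** *This stands.* They apply to HPVss-positive women with normal cytology. Women with abnormal cytology go to colposcopy without the one-year wait, and the document gives no split between the two groups.

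A reader might go further and infer that women will be counted as badly managed because data collection stopped, or that the arms will be biased. The document supports neither. No section says how a woman not yet due is scored. The Sample Size wording defines a different composite and cannot simply be carried over to the second primary outcome. The cut-off is the same date in both arms, and no recall schedule by arm is given.

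**Conclusion.** The concern holds as a mismatch between the follow-up end date, the 12-month participation window and the one-year retest. Follow-up after a first test runs from essentially 0 to 36 months, and this follows from the stated dates alone. If the retest counts toward the second primary outcome, the last women recalled cannot reach it. Under even recall, 2% to 52% of normal-cytology women have a retest that falls after the cut-off, with 23% for a test at month 3 and two months to cytology. The 52% is an upper case in which every woman tests at month 12, and not an expectation. The effect on the outcome among all positive women cannot be sized from the document.

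A difference between arms is possible, through time to testing or through chance imbalance in recall dates, but it is not shown and has no known sign. The first primary outcome is unaffected, since every woman has 12 months after recall. The point should be fixed before the outcome is analysed. It does not undermine the trial as a whole.

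**What to change.** Reconcile Study Design, HPV Test Analysis and Management of Results, and Primary Study Outcomes as follows.

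1. Define the second primary outcome over a fixed window of W months from each woman's positive result, the same in both arms. Score only the guideline steps that fall due inside it, and say explicitly whether the one-year retest is among them.
2. Then choose one of two routes:
   - **Move the extraction.** Take the screening-centre data for this outcome at last recall + 12 + 0.5 + W months, so that every positive woman has the full window. This is W + 0.5 months after the present cut-off. If W covers the retest, W is at least 12, so the extraction comes at least 24.5 months after the last recruitment (about January 2027), 12.5 months later than planned.
   - **Keep the lock date.** Estimate the outcome by cumulative incidence from the positive result, with administrative censoring at the lock and standard errors that account for clustering.

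**Cost.** Neither route needs contact with participants, because the data come from an existing database. The first delays the report on this outcome. The second is somewhat less precise. It also assumes that women censored early, who include the late testers, would have been managed like those observed for longer; analysing by time to testing would help to check this.

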**Figure 1 figure1:**
[figure not shown]
Flowchart of the study. CRCDC-OC: Regional Cancer Screening Coordinating Centre of Occitanie; HPVss: human papillomavirus self-sampling; IRIS: Ilots Regroupés pour l’Information Statistique.

### Study Intervention

The chatbot-based decision aid will be developed using the validated Coulter framework on the basis of the International Patient Decision Aid Standards (IPDAS) [17]. This framework proposes 5 steps (Figure 2): (1) scoping and design, (2) development of a prototype, (3) “alpha” testing with women and clinicians in an iterative process, (4) “beta” testing in “real-life” conditions (field tests), and (5) production of a final version. The chatbot-based decision aid will be tailored to women with a lower education level and will be offered in several languages (the most spoken languages in the Occitanie region) and via several channels.

**Figure 2 figure2:**
[figure not shown]
Model development process for decision aids (adapted from Coulter et al [17]).

### Study Population

Eligible women are those aged 30-65 years who did not respond to an initial invitation letter to have an HPV test collected by a clinician, have not been screened for CC for more than 4 years, and live in the disadvantaged clusters in the Occitanie Region.

Women will be excluded from the study if they have undergone CC screening within the past 4 years, have had a hysterectomy, or have been diagnosed with and are receiving treatment for precancer or CC.

